### Follow-Up or Outcome Measurement

To evaluate the effectiveness and safety of the intervention, information on antibiotic prescriptions, BLAL details, safety indicators, clinical outcomes, microbiological end points, and economic factors will be extracted from the EPR at days 30, 100, and 200. Antibiotic prescription will be monitored throughout the follow-up period. BLAL details will include the outcome of the assessment, along with any newly recorded or relabeled BLALs. The primary outcome is assessed per patient at the predefined time points. Inconclusive outcomes will be single-blinded evaluated by 2 independent infectious disease specialists who, upon disagreement, discuss the outcome with a third senior infectious disease specialist for a consensus. In the absence of doubt regarding the use (or not) of a first-line regimen, the scores are scored (unblinded) by the central study team (n=2). Safety parameters will be evaluated based on antibiotic tolerance and the need to switch antibiotics during treatment. Clinical outcomes will be assessed by measuring the number of days until in-hospital mortality, mortality at 3 months posthospitalization, LOS, and ICU admission rate. Microbiological end points will include colonization and/or infection of methicillin-resistant *Staphylococcus aureus*, vancomycin-resistant *Enterococcus*, and *C. diff.* economic end points, focusing on the societal perspective, will capture the cost of antibiotic treatment and hospitalization, as well as the time and human resources required. However, detailed economic analysis will be the subject of a separate protocol. No patients will be lost to follow-up within participating hospitals, as this study relies exclusively on back-office EPR data extraction. Outcomes are captured through the shared EPR platform “Clinical Workstation” (CWS, Nexuzhealth), a multihospital EPR network used by several tertiary and regional Belgian hospitals. However, antibiotic exposure and readmissions are only captured for hospitals using this EPR network; outpatient antibiotic use and care in nonnetwork hospitals are not captured. Moreover, survival is centrally registered and automatically linked to the patient’s Belgian social security number, allowing us to reliably follow up on this parameter irrespective of subsequent hospitalizations.

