These concerns led to the emergence of invasive delabeling protocols for penicillin allergy labels in the United States and Australia [22,23]. Current approaches use risk stratification based on clinical history and direct challenges (ie, in-hospital, but without prior skin tests) with penicillins or alternative beta-lactams in identified low-risk patients [24,25]. The efforts demonstrate to be cost-effective [22] and impact antibiotic use, shifting more to first-line beta-lactams and narrow-spectrum penicillins [26]. However, a relevant fraction of readministrations was accompanied by a repeat hypersensitivity reaction (3.8%), of which a minority (<1%) were severe [26]. This illustrates the delicate balance between indirect harm through incorrect BLAL and repeat iatrogenicity through invasive delabeling protocols themselves.

An often forgotten step in the delabeling process that encompasses the lowest risk for repeat iatrogeny is noninvasive delabeling. Here, without skin or drug provocation testing, but solely by using patient questionnaires and information from tolerated antibiotic exposures, discordances in the EPR are exploited to the advantage of the patient [9,27-29]. Our group prospectively evaluated in an EU context a noninvasive delabeling protocol in adult internal medicine inpatients with a BLAL [30], combining (1) an allergy-oriented clinical history, (2) an EPR search to identify incorrect BLAL and/or uneventful re-exposures to beta-lactams, and (3) a systematic primary care physician and community pharmacist contact. Using this approach, 38% of BLALs could be delabeled, and another 27% could be refined, largely driven by EPR findings. In the next step, we optimized the EPR search by developing a semiautomated clinical decision support (CDS) tool, designed to identify those patients with documented re-exposure without allergic reaction. A proof-of-concept study, limited to penicillin allergy labels, demonstrated the feasibility and efficacy of this novel CDS tool, identifying nearly 10% of alleged penicillin-allergic patients and showing approximately sevenfold higher odds of delabeling after its introduction [31]. Importantly, the impact on prescription behavior and major clinical outcome parameters is unknown and would be the basis for broad roll-out. Therefore, we propose to perform the first multicenter study on noninvasive BLAL delabeling, using an EPR-embedded, semiautomatic, intelligent “Allergy Fact Checker (AFC)” CDS tool.

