### Sample Size Determination

The main aim of our study is to establish the assumed superiority of using the AFC over SOC in increasing the proportion of patients with first-line antibiotics prescribed. Therefore, we look at the proportion of patients receiving first-line or narrow-spectrum beta-lactam antibiotics within the total number of patients receiving antibiotics. The crossover design accounts for seasonal as well as intra- and interhospital differences in overall antibiotic use. Nevertheless, overall antibiotic use will be monitored at the participating sites during this trial’s period.

The following assumptions were applied.

For the control arm, in a recent retrospective study in UZ Leuven, involving 21,999 patients with pneumonia, pyelonephritis, infections associated with heart, kidney, liver, or lung transplantation; appendectomy; coronary artery bypass grafting; and total knee or hip replacement, we investigated the difference in antibiotic use between patients with and without BLAL [21]. It showed that 10.5% of patients with a BLAL received amoxicillin despite their label. Based on the latter, we estimate that 10% of the patients in the control group already receive first-line antibiotics. We add a 5% increase due to indirect learning of our protocol because we cannot exclude that treating physicians learn to use discordances in the medical file for delabeling or refinement of the allergy labels, independent of our study and AFC tool. Considering around 30% of hospitalized patients receive antibiotics during their stay [34], this brings the percentage down to 4.6% in the control group.

For the intervention arm, we previously showed that our CDS approach has the potential to delabel 38% of BLALs [30]. We add a margin of 5% for physicians or patients who refuse to delabel or be delabeled [9]. Considering around 30% of hospitalized patients will receive antibiotics during their stay, this results in an overall estimate for the intervention group of 9.9%.

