For the intra- and intercluster correlation (ICC), literature indicates a moderate ICC of 0.059 for antibiotic prescription behavior [35,36]. This estimate seems appropriate as moderate differences in antibiotic prescription behavior are expected within and between different physicians at participating sites, which mostly follow the IGGI guidelines, however, with some internal adjustments. Indeed, the most recent point prevalence survey of antimicrobial use and health care–associated infections in Belgian acute care hospitals (results of the global point prevalence survey and European Center for Disease Prevention and Control point prevalence survey) reports 77% compliance with IGGI guidelines [37]. Additionally, 3 participating sites are part of the same Hospital Outbreak Support Team network, that is, Heilig Hartziekenhuis Mol, AZ Turnhout, and AZ Herentals in the Hospital Outbreak Support Team Network Kempen, which has the specific goal to align antimicrobial stewardship. All centers use the same EPR (CWS). The major difference would be expected between UZ Leuven, as an academic hospital, and the other participating sites, as regional hospitals. The AFC is currently only available in the CWS EPR system, and therefore, we were unable to include other academic centers as well. A sensitivity analysis of academic vs regional hospitals will be performed.

Considering the number of hospitalizations per year in each center and a prevalence of 6% of BLALs [8], we expect an inclusion rate of 3285 participants.

Sample size and power calculations were carried out according to the methods described by Hemming et al [38], using the Shiny CRT Calculator [39]. Based on the design given in Figure 1, assuming a discrete time decay (allowing correlations between periods to decay with each period), a within-period ICC of 0.059 and an autocorrelation (ratio of between-period and within-period ICC) of 0.6, this study will have 80% power to detect a statistically significant difference between control and intervention using a 2-sided significance level of 5%, assuming 4.6% and 9.9% of patients to have the primary end point in the control and intervention group, respectively. This sample size calculation is based on patient-level appropriate prescribing proportions and is considered a conservative approximation for the cumulative window-based primary end point.

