In case key assumptions differ importantly from those used in the initial calculations, we will implement a preplanned sensitivity and adaptation strategy focused on nuisance parameters rather than treatment effect estimates. Once the initial target number of inclusions has been reached, we will conduct a blinded (or arm-masked) internal review of (1) overall primary end point incidence, (2) observed within-period ICC and between-period correlation structure, and (3) completeness of follow-up and outcome ascertainment across centers and periods. In parallel, we will run sensitivity power analyses across plausible ranges of ICC or autocorrelation to quantify the robustness of power under departures from assumptions. If this review indicates that statistical power is likely to be compromised (eg, lower-than-expected event rate or higher-than-expected clustering), we will adapt by extending recruitment and/or adding additional crossover periods and/or centers, while keeping the intervention allocation scheme and primary outcome definition unchanged, depending on the available human resources to perform this. Any such modifications will be documented as protocol amendments and reflected in an updated statistical analysis plan. Importantly, to avoid operational recruitment gaps and preserve feasibility, recruitment will continue while this internal review is performed, and the adaptation decision will be based on updated nuisance-parameter estimates rather than interim efficacy signals.

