Secondary endpoints include guideline-concordant beta-lactam use at each individual assessment window (including day 200), delabeling or refinement rate, beta-lactam tolerance, antibiotic switching, ICU admission, readmission, resistant organism outcomes, LOS, mortality, and cost outcomes. Outcomes at day 200 are analyzed as secondary durability measures, as longer-term prescribing may be influenced by label reappearance or documentation changes unrelated to the index intervention. Secondary endpoints will be analyzed using hierarchical mixed-effects models appropriate to outcome type (binary, continuous, or time-to-event), with fixed effects for study phase and period and clustering by hospital. Process evaluation outcomes will be analyzed descriptively.

Predefined subgroup analyses will assess potential effect modification by including phase-by-subgroup interaction terms in the primary model. Subgroups of interest are BLAL type (penicillin vs other labels), reported reaction severity category, time since label registration, infection type (prophylaxis vs therapeutic indication), ICU admission status, and hospital type (academic vs regional). Subgroup analyses will focus on the primary endpoint and are considered exploratory and hypothesis-generating. 

Moreover, because the AFC is expected to influence prescribing primarily through label delabeling or refinement, we will perform an exploratory implementation analysis within the AFC phase. Patients will be classified as with implementation if the BLAL was delabeled or refined after the AFC recommendation, and as not with implementation if otherwise. The cumulative primary endpoint (*sᵢ/nᵢ* up to day 100) will be summarized by implementation status; any between-group comparisons will be considered descriptive and interpreted cautiously, as implementation is a postallocation process measure and may be confounded.

No formal adjustment for multiplicity will be applied. Secondary and subgroup analyses will be interpreted with caution.

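### Beta-lactam tolerance can be scored only in patients given a beta-lactam, a group the AFC is meant to enlarge; reactions should also be compared per enrolled patient.

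*Protocol article*

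**What the plan says.** Under Follow-Up or Outcome Measurement, the article states: "Safety parameters will be evaluated based on antibiotic tolerance and the need to switch antibiotics during treatment". No other measure is called a safety parameter. Both return in the list of secondary endpoints under Statistical Analysis: "delabeling or refinement rate, beta-lactam tolerance, antibiotic switching, ICU admission, readmission, resistant organism outcomes, LOS, mortality, and cost outcomes". These are to be compared between phases with mixed models that include phase and period.

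Other relevant statements:

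- Label changes are extracted, but as label details: "BLAL details will include the outcome of the assessment, along with any newly recorded or relabeled BLALs". The extraction days are 30, 100 and 200.
- Sample Size Determination plans the rise in first-line or narrow-spectrum use, "assuming 4.6% and 9.9% of patients to have the primary end point in the control and intervention group, respectively".
- The Introduction reports, for invasive delabeling and direct-challenge programs, that "a relevant fraction of readministrations was accompanied by a repeat hypersensitivity reaction (3.8%), of which a minority (<1%) were severe". It describes a balance between harm from a wrong label and harm from re-exposure.
- Missing Data treats windows without antibiotics as no opportunity, but only for the window-based prescribing outcomes. Other binary secondary outcomes go to multiple imputation under missing at random.

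**The concern.** The AFC acts by letting more labeled patients receive beta-lactams. In control phases, those exposed are patients treated despite their label. In AFC phases, they are such patients plus those newly delabeled or refined. Comparing tolerance between these groups conditions on something the intervention changes. The groups differ in kind, and the main route to harm, more exposures, drops out of the comparison. Statistical Analysis recognizes the same difficulty for implementation status, which it calls a postallocation measure open to confounding, but places tolerance in an ordinary phase comparison.

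At stake is the balance set out in the Introduction. The prescribing gain arises because more labeled patients receive the drug. The matching harm is reactions among all labeled patients enrolled, and no listed endpoint counts these. A report of similar or better tolerance in AFC phases could be read as reassurance while more enrolled patients had a reaction.

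**Working it through.** **Inputs from the article**

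- Planned first-line or narrow-spectrum use per enrolled patient: 4.6% control, 9.9% AFC (Sample Size Determination).
- Patients receiving antibiotics: 30% in both phases (same section).
- Total sample 3285. An equal split is assumed: 3285 / 2 = 1642.5 per phase.
- Reaction risk per exposed patient, r: the article gives none for the AFC. I take 3.8% from the Introduction as an illustration, with a range of 1% to 10%.

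**Step 1. Reproduce the planned figures.** Control: (10.5% + 5%) × 30% = 4.65%, stated as 4.6%. AFC: (38% − 5%) × 30% = 9.9%, as stated. Ratio: 9.9 / 4.6 = 2.15. Exposed patients: 1642.5 × 0.046 = 75.6 and 1642.5 × 0.099 = 162.6.

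**Step 2. Tolerance with the same r in both phases.** Tolerance = 1 − r = 96.2% in each phase, a difference of 0 whatever the exposure ratio.

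**Step 3. Reactions per enrolled patient = exposure × r.**

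| r | Control, per 1000 | AFC, per 1000 | Expected events | Power, no clustering |
|---|---|---|---|---|
| 1% | 0.46 | 0.99 | 0.8 vs 1.6 | about 8% |
| 3.8% | 1.75 | 3.76 | 2.9 vs 6.2 | about 20% |
| 10% | 4.6 | 9.9 | 7.6 vs 16.3 | about 43% |

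**Step 4. Precision at r = 3.8%.** Risk difference: 3.76 − 1.75 = 2.01 per 1000. Standard error, ignoring clustering: √[(0.001748 × 0.998252 + 0.003762 × 0.996238) / 1642.5] = 0.00183. The 95% interval is 2.01 ± 1.96 × 1.83, or about −1.6 to 5.6 per 1000.

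**Step 5. Switching.** This is scored among patients on any antibiotic. The exposed share of treated patients is 15.5% control and 33% AFC. Suppose every reaction leads to a switch and other switches occur at an assumed background rate b. The switching rate is then b + share × 3.8%.

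| b | Control | AFC | Ratio |
|---|---|---|---|
| 0% | 0.59% | 1.25% | 2.13 |
| 5% | 5.59% | 6.25% | 1.12 |
| 10% | 10.59% | 11.25% | 1.06 |
| 20% | 20.59% | 21.25% | 1.03 |

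Switching moves in the right direction, but background switches dilute the signal.

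**Step 6. Lower risk after AFC review.** Keep the control-type exposures (4.6%) at 3.8% and give the additional 5.3% an assumed risk of 0.5%. Reactions per 1000 in AFC phases: 46 × 0.038 + 53 × 0.005 = 1.75 + 0.27 = 2.01, a ratio of 1.15 to control. Reactions per exposed patient: 2.01 / 99 = 2.0%, so tolerance is 98.0% against 96.2%. Tolerance looks better in AFC phases although reactions per enrolled patient rise slightly.

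**The case against.** Several points count against a stronger reading.

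- **Denominators.** None is written for tolerance or switching, and an unseen analysis plan may fix them. This stands as a caution. Which outcomes serve as safety parameters is nevertheless a protocol choice, and tolerance of a drug cannot be observed in someone who never received it.
- **Switching.** A reader might infer that both measures would show no difference if reactions doubled. That is not supported: switching applies to any antibiotic and would rise, as Step 5 shows. Equal tolerance also requires equal risk per exposure.
- **A doubling of exposure or reactions.** The 4.6% and 9.9% refer to first-line or narrow-spectrum use. Patients in either phase may receive other beta-lactams, so the ratio for total exposure is not given. The 3.8% comes from invasive programs, whereas AFC advice follows documented uneventful re-exposure and a review. Step 6 shows how far the ratio could fall.
- **Other data.** A reader might infer that reactions would go unseen. New or relabeled BLALs are extracted, and ICU admission, readmission and mortality are compared without any stated restriction to exposed patients. None is designated a reaction endpoint, and the last three are not specific to drug reactions.
- **Oversight.** Quality Assurance makes the research team responsible for monitoring safety, so it would be wrong to say that safety is unwatched.
- **The interim review.** It is tempting to ask for reactions by phase at the nuisance-parameter review. The article specifies that review as blinded or arm-masked and says that "the adaptation decision will be based on updated nuisance-parameter estimates rather than interim efficacy signals". A by-phase table would conflict with this, and 3 versus 6 expected events could inform little.

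**Conclusion.** The point holds in a limited form. Of the two designated safety parameters, beta-lactam tolerance conditions on exposure that the AFC is meant to increase, so it cannot show harm that comes from more exposure. Switching shows such harm only weakly. No listed endpoint counts reactions over all enrolled patients.

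Under the 3.8% assumption, the hidden difference is about 2 reactions per 1000 enrolled, or about 3 versus 6 events in the trial. At 1% risk it is about 0.5 per 1000 and at 10% about 5 per 1000. These figures assume equal risk per exposed patient in both phases, an equal split of patients, and exposure limited to the planned first-line or narrow-spectrum use. They illustrate how the measure behaves and do not predict the AFC's risk. The documents do not support the inference that the AFC doubles reactions or that the trial would necessarily declare it safe.

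**What to change.** At final analysis, report by phase the proportion of all enrolled BLAL patients with at least one recorded beta-lactam hypersensitivity reaction up to day 100 and up to day 200, with severe reactions separately. Use new or relabeled BLALs as a supporting source. Count patients without beta-lactam exposure as having no event, and do not impute tolerance for them. Give the risk difference with a 95% CI that accounts for hospital clustering, and present it as estimation, not as a test. Keep tolerance and switching as descriptive measures with their denominators stated. Leave the nuisance-parameter review blinded or arm-masked as planned.

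The cost is endpoint and analysis-plan wording before database lock and one further table. Scoring tolerance already requires reactions to be identified in exposed patients, and the number enrolled is known. The downside is a wide interval and a more modest safety statement. The rate also covers only reactions recorded within the shared EPR network, which the report should say.

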**Methods:**

We are conducting a multicenter, open-label, crossover cluster-controlled study in 9 hospitals in Flanders, Belgium. All hospitalized adults with a BLAL are eligible, excluding patients in palliative care, discharged within 24 hours, or previously enrolled. Each hospital will alternate between intervention (use of the AFC) and control (standard practice) phases, separated by washout periods. The primary endpoint is cumulative guideline-concordant prescribing of first-line and/or narrow-spectrum beta-lactams following local antibiotic treatment guidelines, across predefined care windows up to day 100, expressed as a weighted per-patient proportion. Secondary endpoints include delabeling or refinement rate, beta-lactam tolerance, antibiotic switching, hospital length of stay, in-hospital and 3-month mortality, intensive care unit admission, readmission, multidrug-resistant organism colonization or infection, and costs. Based on prior data, we calculated that a total of 3285 participants are required to achieve 80% power to detect superiority of the intervention (4.6% vs 9.9% appropriate prescribing). Recruitment started in March 2025 and is ongoing.

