## Methods

### Aim

This study aims to evaluate the clinical and economic benefits of a noninvasive CDS tool, critically assessing BLALs the AFC, while following local antibiotic treatment guidelines. Specifically, we will assess its impact on antibiotic use, as well as clinical, antimicrobial, and economic end points in hospitalized adults with BLAL. We hypothesize that a relevant fraction of BLAL can be rationalized by the AFC, thereby improving antibiotic use and costs without impacting morbidity or mortality.

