### Design

A multicenter, open-label, crossover cluster-controlled trial will be conducted to compare the use of our AFC on BLAL (intervention, I) and subsequent antibiotic prescription with current practice (control, C, ie, no AFC). All hospitalized adults with one or more BLAL will be included, except those previously enrolled in this study, discharged within 24 hours, or in palliative care. The primary endpoint is cumulative guideline-concordant prescribing of first-line and/or narrow-spectrum beta-lactams (based on the IGGI [Infectiologiegids/Guide d’Infectiologie] guidelines of the Belgian Society for Infectiology and Clinical Microbiology) across predefined care windows up to day 100, expressed as a weighted per-patient proportion. Within each predefined assessment window, prescribing is scored in an any or ever binary manner, and a cumulative weighted score per patient is calculated across applicable windows. Secondary endpoints include proportion of delabeled and refined BLALs; beta-lactam antibiotic tolerance; need to switch antibiotics; in-hospital and 3-month posthospitalization mortality; LOS; 3-month readmission rate; ICU admission rate; colonization and/or infection with methicillin-resistant *Staphylococcus aureus*, vancomycin-resistant *Enterococcus*, *Clostridium difficile* (*C. diff*); antibiotic and hospitalization cost, time, and resources needed for the AFC; and physician appraisal of the approach.

We chose a mono-faceted intervention without an awareness campaign or educational component (eg, e-learning for physicians on BLAL labeling and delabeling) to evaluate the impact of the AFC itself, enhancing its extrapolation afterward. To correct for interhospital variability, we choose a clustered crossover design. The crossover design also accounts for seasonal variability, for example, in overall antibiotic use.

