### Setting

Patients will be recruited in 9 participating centers across Flanders, that is, the University Hospitals of Leuven (UZ [Universitair Ziekenhuis] Leuven), and the general hospitals of Pelt (Noorderhart Mariaziekenhuis), Mol (Heilig Hartziekenhuis), Herentals (AZ [Algemeen Ziekenhuis (general hospital)] Herentals), Turnhout (AZ Turnhout), Izegem (Sint-Jozefskliniek), Halle (AZ Sint-Maria Halle), Tienen (RZ Heilig Hart Tienen), and Malle (AZ Voorkempen). The expected recruitment period, from First Patient In to Last Patient In, is 11 months, starting March 10, 2025. The total inclusion period from First Patient In to Last Patient Out is expected to take approximately 18 months. The total period of intervention plus follow-up for every single patient depends on the LOS, that is, until 200 days after discharge from the hospital, to collect the secondary end point parameters: in-hospital mortality, 3-month posthospitalization mortality, LOS, and 3-month readmission rate. Patients who are still in the hospital when the end of the recruitment period is reached (estimated February 2026, when the needed sample size was reached) will be excluded. For comparison, in a recent retrospective study in UZ Leuven, involving 21,999 patients with pneumonia, pyelonephritis, infections associated with heart, kidney, liver, or lung transplantation, appendectomy, coronary artery bypass grafting, and total knee or hip replacement, the average LOS in UZ Leuven for patients with BLAL was 21 days (SD 39) [21].

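### Both named mortality endpoints run on the discharge date, so neither counts all deaths over a common time from inclusion, although central vital status would allow it

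*Protocol article*

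**What the plan says.** The Design section of the Protocol article lists "in-hospital and 3-month posthospitalization mortality" among the secondary endpoints. Follow-Up or Outcome Measurement describes the assessment as "measuring the number of days until in-hospital mortality, mortality at 3 months posthospitalization, LOS, and ICU admission rate". The abstract shortens the pair to "in-hospital and 3-month mortality", with no origin for the 3 months. LOS is a secondary endpoint in its own right.

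The Setting section runs each patient's follow-up "until 200 days after discharge from the hospital, to collect the secondary end point parameters". Follow-Up or Outcome Measurement says that outcome data "will be extracted from the EPR at days 30, 100, and 200"; that sentence gives no origin for the days.

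On data sources, the same section says that "survival is centrally registered and automatically linked to the patient’s Belgian social security number", so that death is known wherever the patient is later treated. Missing Data expects no missing mortality data and censors survival outcomes at the last known follow-up.

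Mortality belongs to the hypothesis. The Aim section expects the tool to work by "thereby improving antibiotic use and costs without impacting morbidity or mortality".

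**The concern.** A comparison of deaths between phases is easiest to interpret when every patient is observed for the same time from a starting point that the intervention cannot move. Neither named endpoint has that property.

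- **In-hospital mortality** is observed only during the stay, so its window is LOS, an outcome the intervention may change.
- **Mortality at 3 months after the stay** starts its clock at discharge. If in-hospital deaths are left out, the comparison is confined to survivors to discharge, a group formed after allocation. If they are included, the endpoint holds every death up to its closing date, but that date differs between patients by as much as their stays differ.

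If stays were shorter in the intervention phase, deaths would move from the in-hospital figure to the post-discharge figure with no patient dying earlier or later. One endpoint would look better and the other worse. Splitting the deaths between two endpoints also costs precision in the comparison meant to reassure on mortality.

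**Working it through.** The article gives no mortality rate, so there is no stated figure to reproduce. The size has to be illustrated with assumed death hazards.

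**Inputs**
- LOS: mean 21, SD 39 days (Setting; an earlier single-centre cohort). The lognormal shape is an assumption.
- Death hazard per day from inclusion (assumed): 0.2%, 0.4% or 0.8% to day 30, then 0.1%, 0.15% or 0.2% (low, middle, high). The hazard does not depend on discharge, and the intervention has no effect on it.
- 3285 patients (Sample Size Determination), about 1640 per phase.

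**Step 1: spread of the windows.** σ² = ln(1 + (39/21)²) = 1.493, so σ = 1.222; μ = ln 21 − 1.493/2 = 2.298. The median is exp(2.298) = 10.0 days. The 10th and 90th percentiles are exp(2.298 ∓ 1.2816 × 1.222), about 2 and 48 days. The in-hospital window thus differs by about 45 days across the middle 80% of patients, and LOS + 90 closes between about day 92 and day 138.

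**Step 2: shorten stays and leave dates of death unchanged** (2,000,000 simulated patients, middle hazards):

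| Endpoint | Stays unchanged | All stays 20% shorter | 20% shorter in 10% of patients |
|---|---|---|---|
| In-hospital death | 6.04% | 5.10% | 5.95% |
| Death within 90 days of discharge, survivors to discharge only | 16.28% | 16.64% | 16.31% |
| Death by discharge + 90 days, in-hospital deaths included | 21.34% | 20.89% | 21.29% |
| Death by day 100 from inclusion | 20.15% | 20.15% | 20.15% |

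The last row is 1 − exp(−(30 × 0.004 + 70 × 0.0015)) = 1 − exp(−0.225). It does not involve LOS and cannot move.

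**Step 3: range over the assumed hazards.** In-hospital mortality with unchanged stays is 3.3%, 6.0% and 10.9%. Cutting every stay by 20% lowers it by 0.55, 0.94 and 1.55 points. Cutting 10% of stays lowers it by 0.06, 0.09 and 0.16 points. With a shorter assumed LOS (mean 8, SD 10) and hazards of 0.3% then 0.1% per day, cutting every stay by 20% moves in-hospital mortality from 2.2% to 1.8% and post-discharge mortality among survivors from 12.7% to 12.9%. The direction is the same.

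**Step 4: against sampling error.** The SE of an in-hospital difference at 6% is √(2 × 0.06 × 0.94 / 1640) = 0.83 points before clustering. The shift is 0.94/0.83 ≈ 1.1 SE if all stays change and 0.09/0.83 ≈ 0.1 SE if 10% do.

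**Step 5: deaths counted.** Under the middle hazards, 6.0% of 3285 is about 200 in-hospital deaths; 20.1% of 3285 is about 660 deaths by day 100.

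**The case against.** Most of the case on the other side concerns size and readings that the text does not force, and much of it stands.

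- A reader might infer that patients who die in hospital cannot be scored on the 3-month endpoint. The article does not say so. The wording can equally mean dead by that date, with in-hospital deaths counted. On that reading the selection of survivors disappears and only the moving closing date remains.
- A reader might also infer that discharge is treated as censoring, which would inflate a Kaplan-Meier estimate of in-hospital death. Missing Data names the last known follow-up as the censoring time, and vital status is known after discharge, so the plan states no such rule.
- A 20% cut in every stay is not plausible. The Introduction reports that the tool identified nearly 10% of penicillin-labelled patients in the proof-of-concept study, and Sample Size Determination puts antibiotic use at around 30% of inpatients. Taking 38% delabelled × 30% treated = 11.4% of patients, the in-hospital figure moves only from 6.04% to 5.94%. The LOS input comes from one academic centre and selected conditions.
- Extraction at fixed days, central registration and a time-to-event model are compatible with all-cause survival over follow-up, and the analysis plan may fix origin and scoring. In-hospital mortality is a conventional endpoint. The abstract's shorter label is abbreviation, not contradiction.

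What this leaves is the choice of endpoints. The protocol names two, both tied to discharge. An analysis plan that follows them inherits that anchor, and one compatible with a fixed-horizon endpoint still has to add it.

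**Conclusion.** The point holds as a modest weakness in a secondary safety comparison. Both named mortality endpoints have discharge-dependent windows, LOS is an outcome, the place of in-hospital deaths in the 3-month endpoint is unstated, and under either reading no named endpoint covers all deaths over a common time from inclusion. That is a poor basis for the mortality part of the hypothesis when the allocation is open and nonrandomized.

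The likely bias is small: about 0.1 point on in-hospital mortality if a tenth of stays shorten by 20%, and about 0.9 points only if all do. Both figures rest on assumed death hazards and a lognormal LOS. The gain in deaths counted, about 660 against about 200, rests on the same assumptions. The documents do not support saying that mortality results will be materially distorted, that in-hospital deaths are excluded, or that discharge is a censoring event.

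**What to change.** Before database lock:

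1. Make all-cause death within 100 days of inclusion (and within 200 days), taken from the central registration and counted in all enrolled patients, the main mortality comparison for the hypothesis in the Aim section.
2. Keep in-hospital and post-discharge mortality as descriptive splits, and state whether in-hospital deaths count in the 3-month figure.
3. If time to in-hospital death is modelled, treat discharge alive as a competing event.

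The cost is wording in the endpoint list and the analysis plan. Follow-up to 200 days after discharge already reaches past day 200 from inclusion, so no new data are needed. The one downside is that the main mortality figure becomes slightly less comparable with reports of in-hospital mortality; the descriptive split preserves that comparison.
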